**Methods:**

This is a prospective, unicenter, randomized, unblinded, pre- and postintervention study. The groups will be randomized (MOON vs control) via an electronic case report form. The MOON intervention will be performed 2 times per week for 10 weeks (30 minutes per session). The first 5 weeks (10 sessions) will be conducted face-to-face at the Puerta de Hierro University Hospital, and the remaining weeks will be conducted via the internet at the participants’ homes. The total sample consists of 152 patients aged between 7 and 18 years. All participants have a clinical diagnosis of ADHD under pharmacological treatment. Data collection will be used to obtain demographic and clinical data. The data will be recorded using REDCap. Measures will be made through clinical scales for parents and objective tests of cognitive functioning in patients. Additional information on academic performance will be collected. The study has a power greater than 80% to detect differences. Student *t* test, 2-factor analysis of variance (ANOVA), and Mann-Whitney analyses will be performed according to each variable’s characteristics.

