### Participants

#### Sample

A total of 152 patients (76 cases versus 76 controls) with a clinical diagnosis of ADHD according to the DSM-V (Diagnostic and Statistical Manual of Mental Disorders, Fifth Edition) will be enrolled. All participants will have a clinical diagnosis of ADHD, take ADHD medication, be clinically stable, and have a Clinical Global Impression (CGI) score between 3 and 6 before entering the trial. Medication will not change during the investigation unless changes are required for clinical reasons. A 15% loss rate is expected. The inclusion and exclusion criteria are summarized in Textbox 2.

Participant inclusion and exclusion criteria.Inclusion criteria:Age 7 to 17 years (may turn 18 during the study)Clinical diagnosis of attention deficit hyperactivity disorder (ADHD) in any presentationTaking pharmacological treatment for ADHDAbility to follow verbal instructionsAbility to play a video game (not necessary to play regularly)Clinically stable, with ADHD symptomatology severity based on a clinician-assessed Clinical Global Impression (CGI) score between 3 and 6Exclusion criteria:Patients with severe symptoms (> or equal to 5 CGI) or very mild symptoms (CGI < or equal to 1)Patient at risk of suicide (according to the clinical judgment of the professional in charge of the patient)Motor difficulties that prevent playing the video gameParticipation in other similar studiesIntention to initiate any psychotherapeutic treatment (including cognitive-behavioral therapy) in the next 3 months of the course of participation in the clinical trial

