### Analyses

#### Sample Size Calculation

Based on similar investigations with hypotheses that are centered around the administration of the SDQ [52], our sample size calculation shows the need to perform the study on approximately 152 participants with a diagnosis of ADHD to cover most of the possibilities with a Cronbach α of 0.05 and a statistical power of 80%, taking into account a 15% dropout rate. We performed the sample size calculation to contrast a mean in the control group of 11 points on the SDQ global score versus a 2-point mean drop (symptomatologic improvement) in the experimental group with a pooled SD of 4. This estimate covers other less conservative situations, such as a difference of up to 4 points.

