#### Study Population

The intention-to-treat (ITT) analysis population is defined as participants who are randomized and receive at least 10 sessions, and the per-protocol population is defined as participants who will complete 100% of the training. All analyses will be performed on the premise of the ITT analysis.

A 2-way analysis of variance (ANOVA) will be performed, with time (pre and post) and group (experimental vs control) as factors and each measure as dependent variable. The difference between the study groups will be considered significant when P<.05.

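### Baseline parent SDQ is measured in both arms, but no stated test uses it as a covariate; this loses power (about 10 points at an assumed pre-post correlation of 0.5) without causing bias

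*Protocol article*

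**What the plan says.** The model is fixed under Analyses, Study Population: a two-way ANOVA "with time (pre and post) and group (experimental vs control) as factors and each measure as dependent variable", followed by "The difference between the study groups will be considered significant when P<.05". The Abstract (Methods) gives a wider list: "Student *t* test, 2-factor analysis of variance (ANOVA), and Mann-Whitney analyses will be performed according to each variable’s characteristics". It does not say which of these tests serves the primary endpoint. No section names ANCOVA, a covariate or baseline adjustment.

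Table 1 shows the parent SDQ at inclusion and at the final visit. Primary End Point Analysis defines efficacy as the change in the global score between those two visits.

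Sample Size Calculation is a plain comparison of two means: "a mean in the control group of 11 points on the SDQ global score versus a 2-point mean drop" "in the experimental group with a pooled SD of 4". No pre-post correlation enters it, and it does not say whether the SD belongs to the score or to the change.

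**The concern.** The strongest known predictor of a child's final SDQ is likely to be the same parent's SDQ at day 0. That value is in hand for every randomised child, yet the stated tests either ignore it (a t test or Mann-Whitney test on final scores) or subtract it with a fixed weight of 1 (the change score implied by the time-by-group ANOVA). ANCOVA estimates the weight from the data and is therefore at least as precise, apart from one degree of freedom.

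What is at stake is the sensitivity of the primary test. The Introduction reports that the preceding trial found no significant effect on its primary outcome and gives a larger sample as one response. Precision that costs no extra patients serves the same purpose.

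**Working it through.** **Inputs from the article.** Difference 2 and pooled SD 4 (Sample Size Calculation); 76 per arm (Sample); 15% loss; significance at P<.05; power 80%. **Assumed, because not given:** a two-sided test; pre-post correlation rho, shown over a range; equal variances at the two visits.

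**Step 1. Reproduce the plan's figure.** A two-sided t test with difference 2, SD 4 and 80% power needs 63.8, so 64 per arm. 64/0.85 = 75.3, so 76 per arm and 152 in total. This matches. Conversely, 76 × 0.85 = 64.6; I use 64. The noncentrality is 2/(4 × √(2/64)) = 2.83 and the power is 80.1%.

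**Step 2. What the stated ANOVA tests.** With two time points, the repeated-measures time-by-group interaction is the t test on change scores.

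**Step 3. Variances, with σ the SD of the score.**
- Final score: σ²
- Change score: 2(1 − rho)σ²
- ANCOVA on baseline: (1 − rho²)σ²

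Change score minus ANCOVA is (1 − rho)²σ², which is positive for every rho below 1. Final score minus ANCOVA is rho²σ², which is positive for every rho other than 0.

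**Step 4. Power if SD 4 is the SD of the score** (64 per arm, noncentral t; df 126 for change, 125 for ANCOVA).

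| rho | SD, change | Power, change | SD, ANCOVA | Power, ANCOVA | Gain (points) |
|---|---|---|---|---|---|
| 0.3 | 4.73 | 66.0% | 3.82 | 83.7% | 17.7 |
| 0.4 | 4.38 | 72.7% | 3.67 | 86.5% | 13.8 |
| 0.5 | 4.00 | 80.1% | 3.46 | 90.0% | 9.9 |
| 0.6 | 3.58 | 88.1% | 3.20 | 93.9% | 5.8 |
| 0.7 | 3.10 | 95.2% | 2.86 | 97.6% | 2.4 |
| 0.8 | 2.53 | 99.3% | 2.40 | 99.7% | 0.4 |

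A t test on final scores has 80.1% at every rho, so its loss runs the other way: small at low rho, and 97.6 − 80.1 = 17.5 points at rho 0.7. At rho 0.5 the two unadjusted variances are equal, so the loss is the same for both.

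**Step 5. Power if SD 4 is the SD of the change.** The change-score test then has 80.1% at every rho. The ANCOVA SD is 4 × √((1 + rho)/2):
- rho 0.3: SD 3.22, power 93.6%
- rho 0.5: SD 3.46, power 90.0%
- rho 0.7: SD 3.69, power 86.1%

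**Step 6. No dropout (76 per arm), rho 0.5.** Change score 86.5%, ANCOVA 94.2%, a gain of about 8 points.

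The loss for Mann-Whitney was not computed.

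**The case against.** **The plan meets its own target.** At rho 0.5 the stated analysis has 80.1% power against a target of 80%, so the 10 points are headroom. That stands. If the true between-group difference were 3 points, at the lower end of the 3 to 4 point decrease named in Hypothesis, power at rho 0.5 would be about 99% with either method. The sample size, however, rests on 2 points.

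**The size depends on an assumed correlation.** This also stands. The children are clinically stable and medicated, and the same parent scale is repeated about 12 weeks apart. These features do not favour a low rho, though they do not fix its value. If SD 4 is the SD of the score, the gain over the change score has almost gone at 0.8.

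**A condensed article may leave covariates to an analysis plan.** It may, but this article names its model and its tests, and all are unadjusted. The point concerns a stated choice.

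Three stronger readings are tempting, and the documents do not support them:
- *The primary test misses 80% power.* This holds only if SD 4 is the SD of the score and rho is below 0.5. The article says "a 2-point mean drop (symptomatologic improvement) in the experimental group with a pooled SD of 4" and does not settle which SD that is.
- *Chance baseline imbalance is a further harm.* It is the source of the change score's extra variance and is already counted in the power figures. Baseline is not ignored either, since it enters through the time factor.
- *Every test in the Abstract is a primary test.* The Abstract assigns none of them to the primary endpoint.

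**Conclusion.** The point holds as one of lost efficiency. The time-by-group ANOVA is a valid, unbiased analysis of change under randomisation, but it makes less use of the day-0 SDQ than ANCOVA would. At about 64 evaluable children per arm and rho 0.5, the loss is about 10 points of power (80% vs 90%), whichever SD was meant. Away from 0.5 the size depends on that SD. From rho 0.3 to 0.7 the loss runs from 18 down to 2 points if SD 4 belongs to the score, and from 14 down to 6 points if it belongs to the change. These figures rest on an assumed rho, a two-sided test, equal variances at the two visits, and the interaction being the term tested. It should be changed because the gain needs no extra data, and ANCOVA does well without knowing rho in advance.

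**What to change.** - In Analyses, Study Population, state the primary analysis as follows: the final-visit parent SDQ global score is analysed by ANCOVA with group as factor and day-0 SDQ as covariate, reporting the adjusted between-group difference with its 95% CI and P value.
- Use the same form for the continuous secondary scales measured at both visits.
- Keep the time-by-group ANOVA, if wanted, as a supportive analysis.
- In Sample Size Calculation, state whether SD 4 is the SD of the score or of the change.
- Name one day for the final visit when rewording, since the article gives both D70 and D90 for the SDQ comparison.

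Cost: a wording change and one degree of freedom. No new data and no additional patients.

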#### Demographic and Baseline Characteristics

A data collection notebook will be used to obtain demographic and clinical data. The data will be recorded with electronic CRF (REDCap). Measures to answer the hypotheses will be made through clinical scales for parents and objective tests of cognitive abilities in patients. Additional information on academic performance will be collected.

#### Primary End Point Analysis

The main objective is to test the efficacy of the cognitive training treatment (MOON) in improving emotional regulation in patients aged 7 to 18 years who have a clinical diagnosis of ADHD. The effectiveness is evaluated by measuring the change produced between the baseline evaluation (day 0) and the final evaluation visit (day 90) in the decrease of 3 to 4 points in the global SDQ score evaluated by the parents. A decrease of 3 to 4 points on the postassessment visit (D70) concerning the preassessment visit (D0) will be considered an improvement in emotional regulation based on other similar studies [52].

Subsequently, 3 parent SDQ measures will be assessed: initial assessment (D0), midterm assessment (D45), and final assessment (D90) to evaluate hypothesis 5 (switching from face-to-face to web-based methods does not lead to differences in emotional regulation).

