For the MOON group, the total number of sessions with the video game will be 20 (twice a week, adjusted according to the availability of the participants). Participants in the MOON group aged 12 years and over will perform the video game sessions in VR, while those under 12 years will perform the video game sessions on a computer. All participants in the MOON group will perform the cognitive training with MOON following the same order of the games reflected in Table 2. Each session will have a maximum duration of 30 minutes (approximately 20 minutes of MOON gameplay). The first 10 sessions will be held in person at the hospital. For participants over 12 years of age, the researchers will help to manually calibrate the eye distance of the VR headset to adjust the quality of vision. For those under 12 years of age, researchers will perform computer-based support to ensure proper use and understanding of the video game tasks. The researcher will explain the task, adapting the instructions to each participant’s age. Once the researcher is assured of the understanding of the task, the difficulty level will be raised in a personalized way for each participant. Progress is signaled to the player by leveling up, parameters (eg, hits, errors, time taken), and stars earned (0 star=poor performance, must repeat the level; 1 star=acceptable performance; 2 stars=good performance; 3 stars=excellent) (Figures 2 and 3).

**Table 2 table2:** Gameplay order by sessions.

Mode			Onsite at the hospital																			At participants' homes																		
Sessions			1		2		3		4		5		6		7		8		9	10	11			12		13		14		15		16		17		18		19		20

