**Figure 3 figure3:**
[figure not shown]
The star system in The Secret Trail of Moon (MOON).

Parents in session 10 will receive a flash drive with the video game and training on how to use it at home. The last 10 sessions will take place at the participants’ homes on their computers and will be monitored via the internet by the researchers. Data collected in the game (eg, completed levels, hits, errors, or reaction times) will be automatically sent to the PlayFab (Microsoft Corp) data server. The parents of MOON group participants will be asked in advance to provide their consent for the collection of these data.

For the control group, participants will be followed up with weekly calls to parents during this period. During this follow-up, psychoeducational support about ADHD will be provided to the parents.

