### Hypothesis

Our main hypothesis is that patients with ADHD using MOON will improve their emotional regulation more than the control group. The efficacy will be evaluated by measuring the change produced from the baseline evaluation (day 0) and the final evaluation visit (day 90), aiming for a decrease of 3 to 4 points in the global score of the Strengths and Difficulties Questionnaire (SDQ) filled by the patient’s parents.

As secondary hypotheses, the difference with the control group in measures such as ADHD core symptomatology, cognitive abilities, and academic performance will be assessed. Our secondary hypotheses are listed in Textbox 1.

Secondary hypotheses of the study.H2: Patients with Attention deficit hyperactivity disorder (ADHD) using The Secret Trail of Moon (MOON) video game will improve in core ADHD symptoms compared with the control group.H3: Patients with ADHD using MOON will improve their cognitive functioning compared to the control group.H4: Patients with ADHD using MOON will improve in academic performance with respect to the control group.H5: A change in platform (face-to-face, internet) will not entail differences in emotional regulation.H6: There will be no clinically meaningful side effects associated with the video game.

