#### Udvalg für Kliniske Undersogelser for Patients With ADHD

Udvalg für Kliniske Undersogelser (UKU) is a tool designed to evaluate possible secondary symptoms that happen during the week [49]. This scale is not included in the assessment phases. Only the participants playing VR will have to complete the scale after each cognitive training session.

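### The SDQ visits do not separate the face-to-face and home phases that H5 compares, and the only general side-effect scale named for H6 is given to VR players alone

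*Protocol article*

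**What the plan says.** **H5 (the change of platform makes no difference to emotional regulation).** The Abstract's Methods state: "The first 5 weeks (10 sessions) will be conducted face-to-face". The remaining sessions are at home. Under Procedure, session 10 is when parents receive the flash drive and home training, and session dates may be adjusted to the participant's availability. The same section says: "Participants in the MOON group aged 12 years and over will perform the video game sessions in VR", with younger children on a computer. The last ten sessions take place in participants' "homes on their computers and will be monitored via the internet by the researchers". Primary End Point Analysis schedules the SDQ at D0 and then at "midterm assessment (D45), and final assessment (D90) to evaluate hypothesis 5 (switching from face-to-face to web-based methods does not lead to differences" in emotional regulation). That section and the SDQ description also place the post-assessment at D70. No margin or decision rule is given for H5. The only rule stated, under Study Population, is P<.05 for differences between the study groups.

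**H6.** Textbox 1 reads: "There will be no clinically meaningful side effects associated with the video game". Safety and Adherence Analysis drops the qualifier about clinical meaning and names three instruments: UKU, SDSC and GASA. Table 1 schedules SDSC and GASA at inclusion and at the final visit. It shows the UKU only in the training column. The UKU description says: "Only the participants playing VR will have to complete the scale after each cognitive training session".

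**The concern.** H5 and H6 both assert an absence: no difference between modes, and no meaningful side effects. Such a claim needs measurements that isolate what is being compared, in the people to whom it applies, and enough precision to exclude a difference that matters.

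For H5, an SDQ fixed by calendar day rather than by the switch mixes the two modes. The final SDQ may also include time after training has ended. If imprecision were then read as agreement, H5 could be accepted when one mode does all the work. For H6, the statement covers the video game as a whole, but the scale for general side effects misses the younger computer players and the home half of training. All participants take ADHD medication, for which the Introduction lists insomnia and appetite suppression among the side effects. Without a baseline or control UKU, symptoms recorded on that scale cannot be attributed to the game rather than to the medication.

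**Working it through.** **1. The plan's own figure.** Sample Size Calculation gives "a Cronbach α of 0.05 and a statistical power of 80%, taking into account a 15% dropout rate", and contrasts a control mean of 11 "versus a 2-point mean drop (symptomatologic improvement) in the experimental group with a pooled SD of 4". A two-sided t-test (sidedness assumed) with difference 2 and SD 4 needs 64 per arm. 64/0.85 = 75.3, rounded up to 76 per arm, or 152 in total. The stated figure reproduces. No calculation is given for H5 or H6.

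**2. Where D45 falls.** Ten sessions at two per week take 5 weeks (35 days); twenty take 70 days.

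| Reading of the schedule | Switch | Home days before D45 | Training ends | Untrained days to D90 |
|---|---|---|---|---|
| Training starts D0 | D35 | 10 | D70 | 20 |
| Starts D1 | D36 | 9 | D71 | 19 |
| After one week of pre-evaluation (assumed) | D42 | 3 | D77 | 13 |
| Spread over D1-D90, as Table 1's column heading reads | about D45 | about 0 | D90 | 0 |

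On the first reading, D0-D45 holds 35 face-to-face days and 10 home days (10 × 2/7 = 2.9 sessions). D45-D90 holds 25 home days and 20 days after training. If the final SDQ is at D70 instead, the untrained days disappear but the first interval stays mixed.

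**3. Precision of the phase contrast.** Let C = (mid − baseline) − (final − mid) = 2·mid − baseline − final. With equal SD σ and equal correlation r between visits, Var(C) = σ²(4 + 1 + 1) + 2σ²r(−2 − 2 + 1) = 6(1 − r)σ². Inputs: σ = 4 (protocol), 64 per arm (step 1), r = 0.5 to 0.7 (assumed).

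- SD(C) = 4√(6 × 0.5) = 6.93 at r = 0.5, and 4√(6 × 0.3) = 5.37 at r = 0.7.
- Within MOON, the 95% half-width is 1.96 × SD(C)/√64 = 1.70 or 1.31 points.
- MOON minus control, it is 1.96 × SD(C) × √(2/64) = 2.40 or 1.86 points.

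To put this on the scale of the design effect: if the whole 2-point benefit arose face-to-face and none at home, the between-arm C would be 2 in size. Its standard error is 2.40/1.96 = 1.22 or 1.86/1.96 = 0.95. The chance of P<.05 is Φ(2/1.22 − 1.96) = Φ(−0.33), about 37%, or Φ(2/0.95 − 1.96) = Φ(0.15), about 56%. Even that extreme inequality would be missed in roughly 44% to 63% of trials.

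**4. What changes at the switch.** Under-12s play on a computer throughout, so only the setting changes. From age 12, VR gives way to the home computer, so setting and device change together.

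**5. Coverage for H6.**

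| Group or session | SDSC, GASA | UKU |
|---|---|---|
| MOON, 12 and over, hospital (VR) | inclusion and final | after each session |
| MOON, 12 and over, home (computer) | final visit follows these sessions | none |
| MOON, under 12 | inclusion and final | none |
| Control | inclusion and final (no restriction stated) | none |

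Illustration only: with zero events among n children, the one-sided 95% upper limit is 1 − 0.05^(1/n). If a quarter, half or three-quarters of the 76 randomised to MOON are 12 or over (assumed, before dropout), n = 19, 38 or 57 and the limit is 14.6%, 7.6% or 5.1%. None of these limits applies to under-12s.

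**The case against.** Four points on the other side have force.

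- **H6 has more data than the UKU.** A reader might infer that H6 has no usable evidence outside VR. The documents do not support that: SDSC and GASA are scheduled before and after with no stated restriction by arm, age or device. The UKU is tied to motion sickness from VR, so limiting it to VR has a purpose. What remains is the gap in other side effects. General adverse-event collection may sit in the full protocol, which is not shown.
- **The 10-day offset is one reading.** Flexible dates, a 12-week total that includes the evaluations, and Table 1's D1-D90 heading allow anything from 0 to 10 days. Figure 1, on study duration, is not available. This limits the claim, but variable switch dates are themselves a reason not to fix the SDQ by calendar day.
- **No acceptance rule for H5 is written.** One might infer that a non-significant result would be declared as no difference. The P<.05 rule is stated for group differences, and an H5 rule may be in the analysis plan. The precision in step 3 is therefore a warning about that inference, not an error in a stated rule.
- **The missing usability study is not a safety finding.** The Discussion links it to difficulty levels possibly being poorly adjusted for under-12s. It does not speak of side effects and should not be cited as if it did.

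**Conclusion.** The point holds in limited form, for two secondary hypotheses; the primary comparison is untouched.

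H5: as scheduled, the three SDQ visits do not separate the two phases. The mid SDQ is 0 to 10 days past the switch and, with a D90 final visit, the second interval may include up to about 20 untrained days. Setting and device are inseparable from age 12. A non-significant phase contrast would carry little information: its half-width is about 1.9 to 2.4 points between arms (1.3 to 1.7 within MOON) against a 2-point design effect. This rests on SD 4, 64 evaluable per arm and an assumed common correlation of 0.5 to 0.7.

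H6: sleep and game addiction are covered. General side effects, as measured by the only general scale named, are not covered in under-12s, in home computer sessions or in controls, and there is no baseline. A UKU-based conclusion about the whole game would exceed the data.

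**What to change.** **H5.** Take the mid SDQ at the session-10 visit, which already exists, and on a matched day in controls, whose parents already receive weekly calls. Reconcile D70 with D90 so that the second interval reflects the home phase. Compare the MOON-minus-control change in the first phase with that in the second, and report the estimate with its 95% CI, overall and by age group. Do not conclude no difference from a non-significant test. State that setting and device cannot be separated in those aged 12 and over, and that mode remains tied to order because no MOON participant stays face-to-face.

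Comparing the between-arm difference at the mid visit with that at the final visit would not serve. If both modes work equally and the effect builds evenly (1 point, then 2), that quantity is 1, not 0. Its half-width is 1.96 × 4√(2(1 − r)) × √(2/64) = 1.39 to 1.07, so its upper limit passes 2 although H5 is true.

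**H6.** Give the UKU to all MOON participants, with a baseline and final UKU in both arms. Report rates by arm and age group with upper confidence limits. Otherwise restrict the UKU-based conclusion to VR sessions in those aged 12 and over. Align the two wordings of H6, and Table 1 with the UKU description.

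**Cost.** A small questionnaire burden and one assessment moved to an existing visit. By 26 September 2023, 62 were enrolled and 31 had completed, so data for those already enrolled would be incomplete; 152 − 62 = 90 were still to enter. Restricting the conclusions needs no new data.
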